## Abstract

**Background:**

Post-stroke physical inactivity is explained by several factors related to the stroke, which have been suggested as the causes and consequences of functional declines and health problems. Therefore, it is important to increase physical activity levels and reduce the time spent in low-energy expenditure activities after a stroke. Since the maintenance of cardiorespiratory fitness is a significant predictor of physical activity levels post-stroke, it may be important to investigate whether aerobic training is effective in increasing physical activity levels and reducing the time spent in low-energy expenditure activities in this population. The efficacy of aerobic training on these variables is not well known. The primary objective of this trial will be to investigate the effects of aerobic treadmill training on physical activity levels and on time spent in low-energy expenditure activities in people with stroke. The secondary aim will be to evaluate the effects of the training on cardiorespiratory fitness, endurance, depression, mobility, quality of life, and participation.

**Methods/design:**

A randomized controlled trial, with blinded assessments, will be performed in a community-based setting. Altogether, 22 adults with a diagnosis of stroke (>6 months) who are sedentary or insufficiently active will be included. Participants will be randomly assigned to either: (1) aerobic treadmill training (experimental group, at 60–80% of their heart rate reserve) or (2) walking outside (control group, below 40% of heart rate reserve). Both groups will attend 40-min training sessions, three times per week over 12 weeks, in groups of two to four participants, with a trained physiotherapist. Primary outcomes are physical activity levels and time spent in low-energy expenditure activities (Multi-sensor SenseWear Mini® and Human Activity Profile). Secondary outcomes are cardiorespiratory fitness (peak oxygen uptake VO_2peak_ and ventilatory threshold), endurance, depression, mobility, quality of life, and participation. The effects of the training will be analyzed from the collected data using intention to treat. Between-group differences will be measured by two-way repeated measures ANOVA, considering the baseline, post-training, and 4-week follow-up.

**Discussion:**

The results of this trial will likely provide valuable new information on the effects of aerobic treadmill training on physical activity levels and on time spent in low-energy expenditure activities of individuals with stroke, through changes in cardiorespiratory fitness.

**Trial registration:**

ClinicalTrials.gov, NCT02798237. Registered on 13 June 2016.

**Electronic supplementary material:**

The online version of this article (10.1186/s13063-018-2823-0) contains supplementary material, which is available to authorized users.

## Background

Stroke has a high prevalence worldwide [1] and people with stroke are more likely to require help with mobility, self-care, and household activities [2]. Furthermore, they are 40% more likely to have limitations in performing activities compared to matched controls [2]. Furthermore, people with stroke are at high risk of being affected by other cardiovascular diseases or recurrent stroke, which are often associated with the severity of the stroke [1]. Thus, it is important to develop and implement interventions to prevent and manage the associated post-stroke disabilities and the complications and risk factors associated with recurrent stroke, and to promote functionality [3].

Physical activity has the potential to influence several functional domains and health status in individuals with stroke [3]. Physical activity is defined as any bodily movements produced by the skeletal muscles that result in energy expenditure, such as those performed during activities of daily living at home, at work, during leisure, or transport [4]. Exercise is a type of physical activity with specific characteristics: it is repeatedly performed, in a planned and structured way, to improve or maintain physical fitness [4]. Sedentary behavior, which is part of the physical activity continuum and has an independent impact on health, was recently defined as any behavior performed while awake that involves energy expenditure ≤1.5 metabolic equivalents (METs) while in a sitting, reclining, or lying posture [5].

People after stroke have low physical activity levels and spend more time in low-energy expenditure activities, compared with matched individuals without stroke [6]. After a stroke, individuals spend on average 80% of their time in low-energy expenditure activities [7]. Only 15% engage in light and 5% in moderate-to-vigorous intensity physical activity [7]. Post-stroke physical inactivity is explained by several factors, which are directly and indirectly related to the stroke and have been suggested as the causes and consequences of functional declines and health problems [1, 3, 6, 7]. After a stroke, low physical activity levels are the main consequences of the concomitant presence of cardiovascular diseases and disabilities, such as reduced cardiorespiratory fitness (median of 14 mL kg^-1^ min^-1^, ranging from 8 to 23 mL kg^-1^ min^-1^) [8–10], depression [3], mobility limitations [11], as well as low perception of quality of life [12] and restricted social participation [2]. Besides contributing to physically inactive and sedentary lifestyles, these disabilities can also be aggravated by physically inactivity [3], creating a vicious cycle that dramatically impedes post-stroke individuals in adopting healthy lifestyles. There is evidence that both physical inactivity and time spent in low-energy expenditure activities are risk factors for developing diabetes mellitus and cardiovascular diseases (including stroke), and for overall mortality [13, 14]. For every 25–30 min increase in sedentary time per day, there is a 1% increase in risk of cardiovascular disease for elderly individuals [13]. Therefore, it is important to increase physical activity levels and reduce the time spent in low-energy expenditure activities after stroke.

Investigating the influence of exercise on physical activity levels and the importance of reducing the time spent in low-energy expenditure activities in people with stroke has been suggested in a scientific statement from the American Stroke Association as a future research direction [3]. Any exercise would probably increase physical activity level and reduce sedentary duration on the same day that it is performed. However, it is not known which intervention could effectively improve physical activity. In addition, it is also unknown whether these changes occur in individuals with different baseline levels of physical activity and time involved in low-energy expenditure activities, nor if they are maintained after the cessation of the intervention. Since the efficacy of aerobic training in improving cardiorespiratory fitness in people with stroke has been shown [8–10] and that cardiorespiratory fitness is a significant predictor of physical activity after stroke [15], it may be important to investigate whether aerobic training is effective in increasing physical activity levels and reducing the time spent in low-energy expenditure activities in this population. However, the efficacy of aerobic training on these variables is not well known [3, 9].

Only four randomized controlled trials have investigated the effects of aerobic training on physical activity levels in people with stroke [16–20]. In three trials, no between-group differences were found [17, 18, 20]. In the other trial, the physical activity levels of the experimental group (aerobic training plus lower-limb resistance training and home exercises) improved compared to the control group (no intervention) [19]. Therefore, it is not known whether aerobic training alone is an effective intervention. In addition, in all four trials [17–20], physical activity was not the primary outcome and, in three of these trials, physical activity was assessed using self-reported questionnaires [17–19]. Secondary outcomes are not confirmatory, but exploratory; thus, it is not possible to give much credence to them [21]. Although questionnaires are inexpensive and easy to use [22], their accuracy is questionable, since they can be influenced by recall bias, social desirability bias, and the inability of the participants to estimate the frequency, duration, and intensity of their physical activity [3, 22]. One of the four trials assessed the effects of aerobic training on physical activity levels of people with stroke by the number of steps taken over 48 h measured by an accelerometer [20]. However, there is some doubt about whether the number of steps alone is an adequate measure of physical activity levels, since it does not provide any information regarding important parameters of physical activity, such as intensity or duration [15, 23]. Furthermore, the number of steps does not provide information on upper limb or cycling activities [4]. According to a systematic review, although there is no gold-standard portable monitor that can assess physical activity, a multi-sensor device, such as the one that will be used in the present study, has the potential to improve accuracy, since the data are estimated by multiple sensors [22]. In addition, a multi-sensor device can provide information on frequency, duration, and the intensity of physical activity, including low-intensity and non-ambulatory activity [22–26]. To our knowledge, only one randomized controlled trial has investigated the efficacy of an intervention that was not aerobic training in decreasing the time spent in low-energy expenditure activities in individuals with stroke [24]. The experimental group received four counseling sessions with a message of “sit less and move more,” whereas the control group received the same number of counseling sessions but on calcium intake for bone health [24]. However, no statistically significant between-group differences were found [24]. Therefore, measuring physical activity levels and the time spent in low-energy expenditure activities as primary outcomes using adequate measures, as planned for the present study, is recognizably important in trials with people with stroke [3].

Thus, the primary aim of this trial is to investigate the efficacy of aerobic treadmill training in improving physical activity levels and reducing the time spent in low-energy expenditure activities of people with stroke. The secondary aim is to evaluate the effects of the training on cardiorespiratory fitness, endurance, depression, mobility, quality of life, and participation.

## Methods/design

A superiority parallel-group randomized controlled trial, with concealed allocation and blinded assessments, will be carried out. A trained researcher, blinded to the group allocation, will collect the written consent and the outcome measures at baseline, post-intervention (after the 12-week intervention), and at the 16-week follow-up, i.e., 4 weeks after the cessation of the intervention (Fig. 1). The examiner will be blinded to group allocation, and the participants and the treating physiotherapist will be asked not to share any information about the intervention with the examiner. Moreover, evaluations will be carried out in different places. Participants will be randomly assigned to either (1) aerobic treadmill training (experimental group) or (2) walking outside (control group) (Fig. 2).

**Fig. 1 Fig1:**
[figure not shown]
Schedule of enrolment, interventions, and assessments

**Fig. 2 Fig2:**
[figure not shown]
Flow diagram of the study

This randomized controlled trial was prospectively registered at https://clinicaltrials.gov/ct2/show/NCT02798237 (NCT02798237) and received approval (51454115.6.0000.5149) from the institutional ethical review board. The study commenced in August 2017 and the estimated completion date is December 2018.

### Setting

This study will be carried out in a community-based setting in Belo Horizonte, Brazil.

### Participants

Individuals will be recruited from the general community, by contacting health centers and research groups. They will be included if they are ≥20 years of age, have a diagnosis of stroke (>6 months), are inactive or insufficiently active [27], and have written medical permission to allow them to participate in the study. The classification of the Centers for Disease Control and Prevention will be used to determine if an individual is inactive or insufficiently active [27]. Participants will be asked about the exercises they performed most often over the last 4 weeks, including their frequency and duration [28]. Individuals who report not having practiced any exercise over the last month will be classified as inactive [27]. Those who report that they have performed physical exercise over the last month for at least five times per week for more than 30 min at a moderate intensity or for at least three times per week for at least 20 min at a vigorous intensity will be classified as having moderate or vigorous exercise levels, respectively [27]. The intensity of the exercises reported by the participants will be determined based upon the estimated MET [27]. Exercises performed at vigorous intensity are those with an assigned MET that is greater than 60% of the maximum cardiorespiratory capacity of the individual [27]. To determine 60% of the maximum cardiorespiratory capacity, we use 0.6 × (60 – 0.55 × age) / 3.5 for men and 0.6 × (48 – 0.37 × age) / 3.5 for women [27]. Individuals classified as having moderate or vigorous exercise levels will be excluded from the study. Individuals who report doing physical exercise over the last month that is not classified as vigorous or moderate intensity will be classified as insufficiently active [27]. Exclusion criteria are: (1) cognitive impairments, as determined by the education-adjusted cut-off scores for the Mini-Mental Status Examination depending on the education level of each participant (illiterate: 13 points; elementary and middle school: 18 points; and high-school: 26 points) [28]; (2) an inability to respond to simple verbal commands [29]; (3) an inability to walk independently for at least 10 min, with or without a walking device; and (4) have pain or other disorders precluding their participation.

### Participant withdrawal

Participants may withdraw from the trial for any reason at any time. The investigator can withdraw participants from the study for safety purposes. Missing a maximum of six consecutive sessions will be allowed.

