### Intervention and control

All participants will attend three 40-min sessions per week over 12 weeks [3, 9, 30], in groups of two to four. A trained physiotherapist who has experience with aerobic training will supervise both groups. The exercise intensity will be determined, based upon the results of the cardiopulmonary exercise test [3, 9].

Before and after training, the participants will remain at rest for 10–15 min, during which time their heart rate (heart rate monitor), blood pressure (aneroid sphygmomanometer and stethoscope), and peripheral oxygen saturation (oximeter) will be measured. Heart rate will be continuously monitored. Participants will be asked to report any discomfort and not to undertake any other exercise program during their participation in the present study.

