### Experimental group

The participants in the experimental group will perform 5 minutes of warm-up and cool-down treadmill walking, followed by 30 min of aerobic treadmill training at 60–80% of their heart rate reserve [3, 9]. However, for those with poor exercise tolerance, short exercise bouts (for a minimum of 10 min, until they have completed 30 min) may be given initially, with interspersed rest periods [3, 9]. As their exercise tolerance improves, longer periods of continuous exercise with shorter rest periods will be implemented [3, 9]. The progression of the intensity of the treadmill training will be individualized, depending upon the individual’s ability, rate of perceived exertion, heart rate, and blood pressure responses [9]. If they are exercising on the treadmill below their cardiac training range, they will be requested to increase their speed until they are in their cardiac training zone.

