### Data monitoring committee

The study will not have a data monitoring committee, since aerobic training rarely has adverse effects [9]. However, participants will be monitored during the exercise sessions, to identify any kind of signals or symptoms, such as pain, dizziness, and loss of balance, that would require interruption of the exercise session or their exclusion from the study. In addition, participants will be asked to report any discomfort, which will be registered and reported.

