### Statistical analyses

Each participant will be assigned a unique ID. Two independent examiners, who will be blinded to the group allocation, will enter the data into a computer and verify any missing or apparently wrong values. The original paper forms will be kept in a secure place. The electronic files will be available only to the research team.

An independent examiner, who will be blinded to group allocation, will perform the statistical analysis, using the software SPSS (SPSS Inc., Chicago, IL, USA). Descriptive statistics will be calculated for all outcomes.

The effects of the interventions will be analyzed from the collected data using intention to treat. Data from the last available assessment will be used for missed sessions. Between-group differences will be evaluated using two-way repeated measures ANOVA, considering the baseline, post-training, and follow-up measurements. If there are baseline differences between the groups, analysis of covariance will be used to eliminate the influence of extraneous factors, such as baseline cardiorespiratory fitness, physical activity levels, and time spent in low-energy expenditure activities. The level of significance will be set at 5% and adjusted for multiple comparisons. Data distribution and equality of variance will also be analyzed, to ensure the parametric analysis has been applied correctly.

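### Symptom and safety rules remove people from the study rather than only from training, so real week-12 and week-16 outcomes may be lost selectively, which undermines the intention-to-treat analysis

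*Protocol article*

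**What the plan says.** All references are to the protocol article.

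- *Participant withdrawal* lets participants leave the trial at any time, then adds: "The investigator can withdraw participants from the study for safety purposes". It ends with an attendance limit: "Missing a maximum of six consecutive sessions will be allowed". No consequence of exceeding the limit is given.
- *Data monitoring committee* describes watching participants during sessions for symptoms "that would require interruption of the exercise session or their exclusion from the study". Those are the only two consequences named.
- *Intervention and control* sets the schedule: "All participants will attend three 40-min sessions per week over 12 weeks". Under *Experimental group* the training is "30 min of aerobic treadmill training at 60–80% of their heart rate reserve". Under *Control group*, participants walk outdoors below 40% of heart rate reserve.
- *Statistical analyses* states: "The effects of the interventions will be analyzed from the collected data using intention to treat". It continues: "Data from the last available assessment will be used for missed sessions".
- *Methods/design* gives three assessment times: baseline, after the 12-week intervention, and week 16. Under *Randomization procedures*, allocation follows the baseline measurements.

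**The concern.** Intention to treat needs two things: everyone stays in the assigned group, and outcomes are sought from everyone whether or not they completed the intervention. The article promises the first. Its removal rules work against the second, because for safety and for session symptoms the person leaves the study, not just the training programme. The intermediate state, in which someone no longer trains but is still assessed, is not described.

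The triggers arise after allocation and relate to how well a person tolerates training. The two arms train at deliberately different intensities, and *Discussion* acknowledges that neither participants nor the physiotherapist are blinded. The frequency of removal, and the kind of person removed, could therefore differ by arm. An outcome that was never collected cannot be recovered by any later model; it can only be assumed. With 11 people per arm, a few such losses matter.

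**Working it through.** The article gives no removal rates, so no calculation can prove or disprove the point. The passages are compared first, and arithmetic is used only for scale.

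**1. What each rule ends**

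- Investigator withdrawal for safety: ends participation in the study (explicit, discretionary).
- Symptoms during a session: interrupts that session or ends participation in the study (explicit, two options).
- More than six consecutive missed sessions: consequence unstated. Withdrawal is suggested only by the section heading and the two sentences before it.
- Stopping training while staying in follow-up: not mentioned.

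For reference, the schedule is 3 × 12 = 36 sessions, so the limit of six is 6/36 = 16.7% of sessions, or two weeks.

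**2. What the analysis then uses**

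The carry-forward sentence speaks of sessions. Taking it to mean missed assessments:

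- Removed before the week-12 assessment: the last available value is baseline, so both later values equal baseline and the recorded change is 0.
- Removed after the week-12 assessment: the week-12 value is repeated at week 16.

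The person can thus remain in the assigned arm, with a substituted value.

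**3. Scale**

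- The plan's own allowance: 18 × 1.2 = 21.6, rounded to 22, or 11 per arm. This matches the stated target.
- One person is 1/11 = 9.1% of an arm. The expected 20% dropout is 0.20 × 11 = 2.2, about two people per arm. It is an allowance for numbers and does not address who is lost.

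**4. What carrying baseline forward does to an arm mean**

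Suppose *m* of 11 people are removed before week 12, and *d* is the mean change they would have shown had they been assessed. Then:

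- Shift in the recorded arm mean = −*m* × *d* / 11.
- Shift in the between-group difference (experimental minus control) = (*m*_C × *d*_C − *m*_E × *d*_E) / 11.

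Neither *m* nor *d* is in the article. As an assumed range, let *d* run from 0 to the planning difference of 20 points on the Human Activity Profile (HAP) Adjusted Activity Score:

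- *m* = 1: 0 to 20/11 = 1.8 points in that arm.
- *m* = 2: 0 to 40/11 = 3.6 points in that arm.

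If those removed would have worsened (*d* below 0), the shift reverses and the arm looks better than it was. Losses in the control arm act on the difference in the opposite direction. The sign is therefore open.

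**The case against.** The strongest case against is that the text supports less than it first suggests. Four parts of it deserve an answer.

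- **Attendance.** A reader might infer that people who miss more than six consecutive sessions are withdrawn. The article does not say so; the limit could equally be an adherence standard for training. This stands. What remains is that the rule is incomplete.
- **Contradiction.** A reader might infer that the trial excludes by adherence or tolerance while claiming intention to treat. No section removes anyone from the analysis set, and the carry-forward rule allows a withdrawn person to be analysed as assigned. This also stands: the principle is undermined, not contradicted.
- **Size.** One could suppose that three of 11 are removed from the experimental arm and conclude that a 20-point gain is recorded as 20 × 8/11 = 14.5. That split has no source, and the sum assumes that people who stop training would still have gained the full 20 points. Greater loss in the experimental arm is plausible but not shown: the article says aerobic training rarely has adverse effects and allows shorter bouts for poor exercise tolerance. The objection stands against any such figure.
- **Omitted detail.** A journal article may leave follow-up after stopping training to the full protocol, and supplementary material is cited but not shown. This stands only in part. The concern rests on what the article states, namely withdrawal and exclusion from the study, and not on silence alone. Session interruption is the other option for symptoms, but it does not cover someone who must stop training altogether.

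**Conclusion.** The point holds in a limited form. For safety and session symptoms the article explicitly provides for removal from the study, and it does not separate that from stopping training. For the attendance limit the consequence is unstated. Because the triggers follow randomisation and could differ between arms, real week-12 and week-16 outcomes may be lost selectively and replaced by earlier values. Intention to treat would then rest on carrying values forward for people who could have been measured.

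This rests on two readings: that removal from the study ends outcome collection, which is the ordinary meaning, and that the carry-forward rule is meant for missed assessments. The only firm size is that each person lost is 9% of an arm. Neither the amount nor the direction of bias can be derived from the article. Correction is worthwhile because the trial is small and the loss is largely avoidable: the primary outcomes come from a worn monitor and an interview, which stopping training does not in itself prevent.

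**What to change.** Reconcile *Participant withdrawal*, *Data monitoring committee* and *Statistical analyses*:

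- State what follows when the session limit is exceeded.
- State that stopping or missing training, under whatever clinical rule applies and with that rule unchanged, does not end participation in the study.
- Invite everyone randomised to the week-12 and week-16 assessments, at least the 7-day monitor, the HAP and the questionnaires, unless they withdraw consent to follow-up. Analyse them in the assigned group.
- Word the carry-forward sentence in terms of assessments, so that it is clear which gaps it covers.

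The cost is a change of wording and up to two extra assessments, at times already scheduled, for each of the few participants who stop training. The target of 22 is unaffected.
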